### Cost effectiveness analysis

Addressing whether the program is cost-effective is also important. Our cost-utility analysis will assess the cost per quality-adjusted life-years (QALY) added with the program. The analysis is from the societal perspective such that any cost charged to any stakeholder is counted, including volunteer time. The lower the cost per QALY, the more cost-effective the program is. In the present study, costs for treating schizophrenia and controlling symptoms, *e.g*. VD and family members’ time as well as medication costs, will be weighed against averted costs, *e.g*. medical costs of hospitalization and the social costs incurred by the disruption of family and village life by untreated patients. The QUALY costs – and savings – of the proposed study can then be weighed relative to other medical interventions.

We will estimate QALY using a Markov Chain approach, largely modifying and following Garcia-Ruiz *et al*. [22]. As in Garcia-Ruiz, our model will allow for relapses into schizophrenia while taking medication, discontinuing medication due to side effects, or discontinuing medication due to other reasons.

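### The rule that a lower cost per QALY is always better carries no sign condition and can misorder results if net cost is negative or QALYs are not gained

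*Protocol article*

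**What the plan says.** Everything relevant stands in one paragraph of the protocol article, under Cost effectiveness analysis.

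- The measure is a ratio: "Our cost-utility analysis will assess the cost per quality-adjusted life-years (QALY) added with the program".
- The perspective is broad: "The analysis is from the societal perspective such that any cost charged to any stakeholder is counted, including volunteer time".
- The reading rule is "The lower the cost per QALY, the more cost-effective the program is". It has no condition on the sign of the cost or of the QALY difference.
- Programme costs (the article's examples are the time of village doctors and families, and medication) "will be weighed against averted costs, *e.g*. medical costs of hospitalization and the social costs incurred by the disruption of family and village life".
- The intended use goes beyond the two arms: "The QUALY costs – and savings – of the proposed study can then be weighed relative to other medical interventions".

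The paragraph gives no cost, QALY gain or value per QALY.

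**The concern.** A ratio of incremental cost to incremental QALYs can be read as lower is better when both are positive. The paragraph defines a net cost that can fall below zero, because averted costs are offset against programme costs, and it speaks of savings. Hospitalization days are among the outcomes named in the trial's hypothesis (Hypotheses and conceptual model), so averted hospital cost is a real component and not a formality.

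If net cost is negative, a larger health gain at the same saving moves the ratio towards zero, which the stated rule reads as worse. If the QALY difference is negative, opposite results can share one ratio. What is at stake is how the economic result is read when it is set beside other interventions, and how any uncertainty range that crosses zero in cost or QALYs is read. The Discussion hopes that the cost-effectiveness evidence will help bring about policy change, so the reading matters to the intended audience.

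**Working it through.** The article gives no figure to reproduce. The check is algebraic, then illustrated with assumed values.

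**Definitions.** ΔC is incremental cost (programme costs less averted costs), ΔQ is incremental QALYs, both against care as usual. The ratio is R = ΔC/ΔQ. Net monetary benefit is NMB = λ × ΔQ − ΔC, where λ is the value placed on one QALY.

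**Algebra.** The slope of R in ΔQ is −ΔC/ΔQ².
- If ΔC > 0, the slope is negative: more QALYs lower the ratio, as the rule needs.
- If ΔC < 0, the slope is positive: more QALYs at the same saving raise the ratio, so the rule prefers the smaller gain.
- The slope of R in ΔC is 1/ΔQ. At equal positive ΔQ a larger saving still gives a lower ratio, so that comparison is ordered correctly even when net cost is negative.

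**Illustration (all values assumed; monetary units arbitrary).**

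| Option | ΔC | ΔQ | R = ΔC/ΔQ | NMB, λ = 5,000 | NMB, λ = 20,000 | NMB, λ = 50,000 |
|---|---|---|---|---|---|---|
| A | −1,000 | 0.10 | −10,000 | 1,500 | 3,000 | 6,000 |
| B | −1,000 | 0.20 | −5,000 | 2,000 | 5,000 | 11,000 |
| C | −1,000 | 0.02 | −50,000 | 1,100 | 1,400 | 2,000 |
| D | −2,000 | 0.10 | −20,000 | 2,500 | 4,000 | 7,000 |
| E | 1,000 | −0.10 | −10,000 | −1,500 | −3,000 | −6,000 |
| F | 1,000 | 0.10 | 10,000 | −500 | 1,000 | 4,000 |
| G | −1,000 | −0.10 | 10,000 | 500 | −1,000 | −4,000 |

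For example, NMB for C at λ = 5,000 is 5,000 × 0.02 + 1,000 = 1,100.

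- A, B and C share the same saving. The right order is B, A, C; the rule gives C, A, B.
- A and D share the same gain. The rule ranks D first, correctly.
- A and E have the same ratio, although A saves money and gains QALYs while E costs money and loses them.
- F and G have the same positive ratio, although one buys QALYs and the other gives them up for a saving. Their NMB values have opposite signs at every λ shown.

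**How often, under assumed ranges.** Pairs of options were drawn at random (200,000 per setting), with ΔQ uniform from 0.01 to 0.30 and ΔC uniform between 0 and 2,000, or between −2,000 and 0.
- Both positive: among pairs where one option was better on both cost and QALYs, the rule reversed none. Over all pairs it disagreed with NMB in about 9%, 16% and 22% at λ = 5,000, 20,000 and 50,000. None of those disagreements involved a pair with a clear winner; all were trade-offs.
- Negative net cost, positive gain: the rule reversed about 47% of the pairs with a clear winner, and disagreed with NMB in about 43%, 63% and 69% of all pairs at the same three values.

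These percentages depend on the chosen ranges and are not estimates for this trial.

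**The case against.** The strongest reply has four parts.

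First, the trial compares one programme with care as usual. If the village-doctor arm saves money and gains QALYs, it dominates, and no ordering of ratios is needed. This stands for a clear point estimate. It does not cover the stated comparison with other interventions, nor uncertainty that spans zero, and the paragraph leaves the rule unrestricted.

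Second, the sentence is an explanatory gloss in a condensed article, and the treatment of dominance, thresholds and uncertainty may sit in a fuller plan. The absence of those details is indeed no finding here. What remains is a statement the article does make, which is too general for the net cost defined in the same paragraph.

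Third, the measure is framed for QALYs added, so a QALY loss may lie outside what the sentence claims to rank. That is a fair reading and weakens the part about options E and G. It leaves the negative-cost case, where QALYs are gained, untouched.

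Fourth, a reader might infer that the plan expects, or that the sponsor hopes for, a net saving. The text does not support this. It offsets averted costs and mentions savings, but nowhere says that these will exceed the cost of village-doctor time, family time and medication. The Discussion hopes for evidence of health benefit and cost-effectiveness, which is not the same as a net saving.

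**Conclusion.** The point holds in limited form. The stated rule can misorder results once net cost is negative or the QALY difference is not positive, and the article's own definition of net cost leaves the first case open.

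It would be too strong to say that the rule always gives the wrong order when costs are saved: at equal QALY gain a larger saving is still ranked correctly, and under the assumed ranges a little over half of the clear-cut pairs were ordered correctly. It would also be too strong to say that the conclusion on village doctors against care as usual would be wrong.

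The size cannot be given in the trial's own terms, because no cost, QALY gain or value per QALY is stated; the algebra needs none, but every figure above is assumed. The effect is confined to the secondary economic analysis, mainly the comparison with other interventions and any uncertainty that spans zero. The compliance outcomes, the sample size and the treatment-effect model are untouched. This is a minor correction that is worth making.

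**What to change.** In the Cost effectiveness analysis section:

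1. Limit the sentence to the case where incremental cost and incremental QALYs are both positive.
2. Report incremental cost and incremental QALYs separately in every case.
3. Outside that case, report dominance where one arm is better on both, or incremental net monetary benefit over a stated range of values per QALY. Dominance does not settle a saving with a QALY loss, so that case needs net monetary benefit.

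The cost is that a range of values per QALY must be named in advance. The same cost and QALY data serve, and nothing in design or data collection changes. The choice of method for uncertainty, including how to carry it through the planned Markov model, is a separate matter that this correction does not settle.

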### Pilot study

A pilot study will be conducted in two villages (A and B) before the main project.

### Structured training course

During the pilot study, we will develop a three-day training course for VDs and a four-hour research study and treatment familiarization course for families of patients with schizophrenia. These initiatives will build on our previous experience in developing training courses and will also enlist expert consultation. The training courses will be implemented in the two pilot study villages to be selected by PI, matching the two villages with as much similar characteristics as possible, and feedback from experts and trainees will be collected for continuous quality improvement.

### Methods for distributing antipsychotics

In village A, the VD will distribute antipsychotics to family members on a weekly basis for two months. In village B, patients will receive their medicine in the village clinic every day for DOT. These medication distribution methods will be alternated in villages A and B after two months, so that the total time during which medication distribution is facilitated by VDs will be four months. Feedback on these distribution methods will be collected from participating patients, family members, and VDs in structured focus group discussions. The more feasible distribution method will be determined based on these structured discussions.

### Case-management protocol

A preliminary case-management protocol for VDs will be implemented in villages A and B for four months. The protocol for VD management of patients with schizophrenia will be finalized following the structured discussions described above.

### Reliability and validity of instruments

The reliability and validity of instruments to be used in the baseline survey and in follow-up investigations will be examined during the pilot study. Reliability measures will include test-retest reliability and internal consistency. Validity measures will include structural validity, differences among patients with different age and educational levels, and changes observed consequent to VD case management.

### Sample size validation

Assumptions in calculating sample size will be tested using data collected in the pilot. We will adjust our final sample size accordingly and as necessary.

Figure 2 below summaries the main activities for the pilot and main studies.

**Figure 2 F2:**
[figure not shown]
Main activities of pilots and main project.

### Trial status

The trial started its pilot phase in Sankou and Gugang townships of Liuyang Municipality in July 2013. We are currently in the process of collecting the data from the pilot study.

## Discussion

This randomized controlled study of the role of VDs in managing severely ill mental health patients is the first of its kind in China. We anticipate that VDs living and practicing close to the community, despite their relatively limited medical training, will prove to be valuable assets in improving mental healthcare in low resource areas. Furthermore, this research will help define the role of alternative healthcare workers and lay persons more generally in managing chronic illnesses in areas where access to specialist care is either difficult or unavailable. As this problem is not unique to China, lessons gleaned from this study will likely extend to populations around the globe.

Previous research has suggested various means to improve drug compliance [23]:

1. Empowering patients by involving them in treatment decisions.

2. Improving supervision of patients through a multi-disciplinary team approach.

3. Keeping drug regimes simple and giving close attention to side effects.

4. Improving patient education on medication and side effects, and involving family and friends of the patient in treatment and compliance.

5. Attending to the logistical and administrative aspects of treatment by reducing waiting time, selecting treatment locations preferred by the patient, arranging transportation, and so forth.

Our intervention was designed with these means in mind, with VDs playing a pivotal role in facilitating cooperation among patients, family members, and psychiatrists, while themselves providing essential services in educating patients and their families, supervising treatment (particularly with respect to patients’ drug taking) and monitoring for signs of relapse and other developments requiring referral. Living and working in the same village as patients and their families, VDs are easily accessible to patients and likely have already established a bond of trust. With proper training in case management, their current role as providers of basic medical and preventive care can be expanded to include patient education in, and cooperative treatment and monitoring of, mental illness, thus extending the reach of psychiatry into the rural environment. While our analysis is not sufficiently fine-grained to detect the effect of the various individual strategies listed above on drug compliance, it will deliver substantial data on how VDs function in delivering, coordinating and facilitating a case management protocol in which these strategies are mobilized to improve patient outcomes.

The strength of the proposed RCT is its potential to provide high level evidence on the role of VDs in managing schizophrenia, but the proposal has limitations. Our chief concern has been documenting compliance which, when self-reported by patients, is problematic insofar as patients may be reluctant to report poor compliance. With VDs counting pills, directly observing drug-taking and corroborating compliance with family members, we expect that our study will more likely assess the true treatment situation. A further limitation is that our project piggy-backs on the existing free antipsychotic medication program in Liuyang Municipality; thus, the results may not be fully generalizable to populations in communities where Project 686 has not been implemented. Finally, we must recognize that the Chinese healthcare system has yet to compensate VDs financially for the extra effort involved in providing mental health services. We are hopeful that our research will provide evidence of the public health benefit and cost-effectiveness of employing VDs in the management of serious mental health problems, which may in turn facilitate policy changes in creating system incentives for care-givers who provide these services.

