**Methods/design:**

We will conduct a cluster randomized controlled trial in 40 villages in Liuyang, Hunan Province, China, home to approximately 400 patients with schizophrenia. Half of the villages will be randomized into the treatment group (village doctor, or VD model) wherein village doctors who have received training in a schizophrenia case management protocol will manage case records, supervise drug taking, educate patients and families on schizophrenia and its treatment, and monitor patients for signs of relapse in order to arrange prompt referral. The other 20 villages will be assigned to the control group (case as usual, or CAU model) wherein patients will be visited by psychiatrists every two months and receive free antipsychotic medications under an on-going government program, Project 686. These control patients will receive no other management or follow up from health workers. A baseline survey will be conducted before the intervention to gather data on patient’s socio-economic status, drug compliance history, and clinical and health outcome measures. Data will be re-collected 6 and 12 months into the intervention. A difference-in-difference regression model will be used to detect the program effect on drug compliance and other outcome measures. A cost-effectiveness analysis will also be conducted to compare the value of the VD model to that of the CAU group.

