## Methods

### Sampling and cluster randomized controlled design

We will conduct a cluster randomized controlled trial involving a sample of rural schizophrenia patients in Liuyang Municipality, Hunan Province, China. Criteria for the sample include:

1. Resided in one of the administrative rural villages of Liuyang Municipality for the past year.

2. Diagnosed by psychiatrist as having schizophrenia.

3. Registered for free medication under Project 686.

Due to our long time working relationship with the local government in Liuyang, they have agreed to assist us in the random selection of villages. A total of 40 administrative villages will be selected out of 318 administrative villages at random. We will use the statistical software package STATA to generate 40 random numbers. All villages will be randomized into two groups (the intervention arm and the control arm) by block sampling (block size = four). The randomization will be based on villages rather than individuals. Due to the nature of our experiment, the allocation will not be blinded for the service providers, patients and interviewers, but those who analyze the data will be blinded for the group information. The co-PI of this project, who is a statistician, will be responsible for the random allocation sequence and the assignment of clusters to interventions.

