### Intervention – VD model

In the VD model, village doctors will receive training in case-management of villagers with schizophrenia using a protocol developed in the pilot study. The three-day training will feature mental health knowledge, case-management skills, and directly observed therapy (DOT). The format will be tailored to the competencies and expectations of VDs. Family members of patients will receive four hours of psycho-educational coaching on how to support patients and cooperate with the village doctor. VDs will participate in the case management protocol for one year and will receive instruction on antipsychotic therapy from visiting psychiatrists at the time of bimonthly drug dispensing.

Specifics of the VD model are given below.

Per Project 686 protocol, psychiatrists dispense drugs, but provide no other services and do not engage family members in the care of patients. In our VD treatment model, VDs cooperate with Project 686 psychiatrists and also reach out to family members to manage patients and provide the following five services:

1. Develop and maintain case files for every schizophrenia patient.

2. Store and distribute antipsychotics to family members on a weekly basis, or directly observe drug-taking (DOT) at the village clinic on a daily basis.

3. Accompany patients and family members on bimonthly visits to psychiatrists for drug dispensation in order to participate in assessing patients’ mental status and explain treatment plans to patients and their families.

4. Record patients’ medication-taking behavior weekly.

5. Identify signs of relapse in order to provide prompt referral services.

To incentivize VDs’ participation, we have obtained preliminary approval to include VDs’ case management efforts in their annual performance review, and will provide a modest fee for VDs for their time and effort.

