### Procedures

Following a pilot study (see Section below), 40 villages (excluding the pilot study villages) will be randomly selected in Liuyang Municipality. We will conduct a baseline survey of patients with schizophrenia in the villages, collecting data on social demographics, compliance rates, clinical characteristics, and outcome measures. Researchers will explain the research to participants and obtain written informed consent from both patients and family member. And after the randomization, VDs and family members of patients will receive training and education in the 12-month case management protocol as noted in Section above. Researchers will visit VDs every month during the first three months of the study and every three months thereafter for the remaining nine months of the study, obtaining feedback and giving follow-up instructions, and recording and monitoring VDs’ case management work via questionnaire.

In the CAU model, control villages will continue to receive bimonthly visits by psychiatric professionals, who will dispense free antipsychotics per existing Project 686 protocol. No other interventions will be introduced.

Follow-up interviews will be conducted with patients in both VD and CAU model villages at 6 months and 12 months into the intervention, collecting the same data as that collected at baseline (see below).

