### Instruments

Four types of statistics will be collected at baseline and at 6 months and 12 months into the study:

Socio-demographic characteristics: age, sex, education level, marital status, work, economic status, domestic situation (living alone, with family, or with friends).

Clinical characteristics: years of illness, number of bed days in psychiatric hospital in previous two years.

Compliance: This is our primary dependent variable measure. The binary variable Drug Compliance (DC) will be recorded by interviewing patients and their family members. We define as ‘compliant’ patients who, over the past month, have taken all pills as prescribed; otherwise, patients are recorded as ‘non-compliant.’ We will report 1-month, 3-month, 6-month and 12-month compliance as the proportion of patients achieving compliance over the total number of patients. In addition, a continuous variable Drug Compliance Score (DCS) will be used to measure medication compliance. The DCS score will be measured by dividing the actual number of pills taken by the total number of pills prescribed multiplied by 10 over a given period of time, with scores ranging from 0 (complete non-compliance) to 10 (complete compliance). For example, if a patient over the past month took 20 pills out of 100 prescribed, his compliance will be (20/100) × 10 = 2 for the past month.

Clinical/outcome measures: Four types of measures will be collected.

Symptoms score: Schizophrenia is often described in terms of positive and negative (or deficit) symptoms. Negative symptoms respond less well to medication [20], particularly to the antipsychotics that are typically used for cases in our research. Therefore, we will concentrate on the positive symptoms as these correlate more strongly with medication compliance. The Brief Psychiatric Rating Scale (BPRS) will be used to evaluate positive symptoms. The BPRS is an 18-item rating scale that has been widely used in psychiatric practice and research in China, and has good to excellent reliability and validity.

Social functions: We will use the global assessment of functioning (GAF) scale, in which a score of 0 to100 is converted to a disability weight ([100-GAF score]/100). Patients with a disability weight of 0.40 or greater are classified as moderately to severely disabled.

Quality of life score: We will use the QALY weights developed by Lenert *et al*. [21].

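### The Discussion relies on village-doctor pill counts and observed dosing, possible only in the VD arm, to safeguard a primary outcome that the Methods take from one common interview, and the two are not reconciled

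*Protocol article*

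**What the plan says.** All places are in the Protocol article.

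- **Instruments** says of compliance: "This is our primary dependent variable measure". For the binary measure: "The binary variable Drug Compliance (DC) will be recorded by interviewing patients and their family members". A patient counts as compliant only if every prescribed pill in the past month was taken. For the score: "The DCS score will be measured by dividing the actual number of pills taken by the total number of pills prescribed", times 10. No source is given for the number of pills taken.
- **Procedures**: "Follow-up interviews will be conducted with patients in both VD and CAU model villages at 6 months and 12 months", with the same data gathered as at baseline.
- **Discussion** names the documentation of compliance as the main limitation, because patients may hide poor compliance, and answers: "With VDs counting pills, directly observing drug-taking and corroborating compliance with family members, we expect that our study will more likely assess" what really happened.
- **Intervention – VD model** lists weekly distribution or daily observed dosing, and a weekly record of medication-taking, among the services VDs provide. It adds that the trial "will provide a modest fee for VDs for their time and effort", and that there is preliminary approval to include case management in their annual review.
- **Abstract, Methods/design**, on the control arm: "These control patients will receive no other management or follow up from health workers".
- **Sampling and cluster randomized controlled design**: "the allocation will not be blinded for the service providers, patients and interviewers". Only the analysts are blinded.

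**The concern.** The Methods describe one interview applied alike in both arms. The Discussion defends the validity of the same outcome with checks that can exist in one arm only and are made by the people delivering the intervention. A reader cannot tell whether those checks feed DC or DCS.

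Any difference between arms in how non-compliance is detected passes directly into the treatment effect. The direction is open. Pill counts could expose missed doses only in the VD arm and shrink the effect. Favourable VD records could inflate it. Because one missed pill makes a patient non-compliant for DC, unequal detection matters more than it would for a coarser measure.

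Blinding the analysts does not help, since the error is already in the data. Nor does the change-from-baseline model: the baseline survey precedes the intervention, so VD information would affect only the follow-up value, and only in one arm.

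**Working it through.** **1. The texts side by side**

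| Item | VD arm | Control arm |
|---|---|---|
| Patient and family interview (Instruments, Procedures) | yes | yes |
| VD weekly record (Intervention – VD model) | yes | no |
| VD observed dosing (Intervention – VD model, as one of two options) | possible | no |
| VD pill counts (Discussion only) | yes | no |
| Interviewer blinded | no | no |

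No section says that VD records enter DC or DCS, and none says that they do not. Two details keep the question open. The DCS pill number has no stated source. Instruments also promises 1-, 3-, 6- and 12-month compliance, while patient interviews take place only at baseline, 6 and 12 months. If 1 and 3 months are time points rather than recall periods, the only researcher contacts described near them are visits to VDs.

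**2. Reproducing the plan's sample size**

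Inputs from the sample size sections: two-sided 0.05, power 80%, DC 0.5 against 0.7, ICC 0.1, 10 patients per village, 10% drop-out.

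- n per arm = [z₀.₉₇₅√(2p̄(1−p̄)) + z₀.₈₀√(p₁(1−p₁)+p₂(1−p₂))]² / (p₂−p₁)² = [1.960√0.48 + 0.842√0.46]² / 0.04 = 93
- Design effect = 1 + (10−1)×0.1 = 1.9
- 93 × 1.9 = 176.7 per arm, so 18 villages per arm, 36 villages and 360 patients
- 360 / 0.9 = 400

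This matches the plan, and the same formula gives all nine rows of Table 1.

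**3. Scale of the possible bias**

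The document gives no misclassification rates, so those below are assumptions shown over a range. The calculation is a normal-approximation test of two follow-up proportions. There are 200 × 0.9 = 180 analysed per arm and the plan's design effect of 1.9, so effective n = 180 / 1.9 = 94.7 per arm. With d = p₂ − p₁, se₀ the pooled and se₁ the unpooled standard error:

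R = 1 − Φ((1.96·se₀ − d)/se₁) + Φ((−1.96·se₀ − d)/se₁)

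Without misclassification, R is 80.7% for 0.5 against 0.7 and 5.0% under no effect.

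*(a) No true effect, DC 0.5 in both arms.* A share f of VD-arm non-compliers is credited as compliant beyond any such error in the control arm, so the observed VD rate is 0.5 + 0.5f.

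| f | Observed VD rate | Rejection rate |
|---|---|---|
| 5% | 0.525 | 6.4% |
| 10% | 0.55 | 10.6% |
| 20% | 0.60 | 28.2% |
| 30% | 0.65 | 55.2% |
| 40% | 0.70 | 80.7% |

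For f = 20%: (1.96×0.0723 − 0.10)/0.0719 = 0.58, which gives R = 28.2%. At 40% the whole planned difference would be artefact.

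*(b) True DC 0.5 against 0.7.* The VD arm is verified, and a share f of control non-compliers over-report.

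| f | Observed difference | Power |
|---|---|---|
| 10% | 0.15 | 56.9% |
| 20% | 0.10 | 30.2% |
| 30% | 0.05 | 11.3% |
| 40% | 0.00 | 5.0% |

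For f = 20%: (1.96×0.0693 − 0.10)/0.0689 = 0.52, which gives R = 30.2%.

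**The case against.** The strongest reply is that the operative text is in the Methods: one interview of patients and families, in both arms, collecting the same data at each round. The Discussion sentence expresses an expectation in a limitations paragraph, and the VD's recording duties are listed as services, not as data sources.

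Much of this stands. A reader might infer that the primary outcome is in fact measured differently in the two arms, and by the paid deliverers of the intervention. The document does not support that, because nothing routes VD data into DC or DCS. Three further points limit the case:

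- Family report is available in control villages too. Only the VD's own counts, observation and corroboration are confined to one arm.
- The fee is for time and effort, and the performance review has only preliminary approval. Neither is tied to recorded compliance.
- The lack of interviewer blinding is disclosed and attributed to the nature of the experiment. Coached families would often reveal their arm, so masking could only be partial.

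The illustration also has a limit. Self-report can differ by arm even under a common interview, so a single source would reduce this bias without removing all of it.

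What the reply does not meet is the Discussion's claim itself. It is about how well the study assesses compliance, and it relies on checks that control villages lack. If the Methods govern, that claim offers no protection. If the claim is true, the Methods description is incomplete.

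**Conclusion.** The point holds as an unreconciled contradiction about how the primary outcome is ascertained, not as proof of differential measurement. Either VD data inform DC or DCS, and ascertainment differs by arm in an unknown direction, or they do not, and the stated answer to the main limitation falls away, leaving unblinded interviews.

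Modest errors would matter. An over-credit of 10% of VD-arm non-compliers roughly doubles the type I error, and 20% takes it to about 28%. In the other direction, over-reporting by 20% of control non-compliers halves the observed difference and cuts power from about 81% to about 30%. These sizes rest on assumed error rates, 180 analysed per arm, ICC 0.1 and a comparison of follow-up proportions. The planned sample size is not in question. Severity: should-fix.

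**What to change.** 1. State that DC and DCS at baseline, 6 and 12 months, and any 1- and 3-month compliance reported, come from one identical patient and family interview in both arms.
2. State that VD pill counts, observed-dosing logs and weekly records are process data, do not enter outcome scoring and are not shown to interviewers.
3. Use outcome interviewers who do not make the monitoring visits to VDs, and do not tell them the village's allocation.
4. Remove or correct the Discussion claim that VD checks improve the assessment of compliance, and state that the remaining self-report bias may differ by arm.

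The cost is protocol wording and the assignment of existing staff. The trial status section places the trial in its pilot phase, so this can be settled before the main baseline survey. The downside is that VD records can then not be used to correct self-report, and masking of interviewers will sometimes fail in the field.
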